### Study procedure

Table 3 summarizes participant procedures in the study. The duration of the study is expected to be six months from May 2010 to October 2010.

**Table 3 T3:** Stages of study procedure

Stage of study	Procedure
Online registration	- Participant registration, study consent and Healthy.me tutorial (self-completed online)

Baseline	- Pre-study survey (self-completed online)
	- Data from de-identified clinical audit from previous 12 months: electronic extraction (collected post-study)

Follow-up procedures	- Monthly one-minute surveys (self-completed online)
	- Post-study survey (self-completed online)
	- Patterns of *Healthy.me *use (computer logs and data entered by participants)
	- De-identified clinical audit at study completion: electronic extraction (collected post-study)

Email will be the primary channel to communicate with participants for study information and reminders about survey completion. From the time participants are recruited until study completion, all participants (control & intervention) will receive an email in the first week of each month to complete a one-minute survey about their health in the past month. At study completion, all participants will receive an email asking them to complete a post-study survey. Two follow-up emails five days apart from each other will be sent to remind those who have not completed each survey to ensure the completeness of data collection.

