**Methods/Design:**

A 2010 CONSORT-compliant randomised controlled trial with a two-group parallel design will assess the efficacy of a web-based PCHMS called *Healthy.me *in facilitating the uptake of influenza vaccine amongst university students and staff. Eligible participants are randomised either to obtain access to *Healthy.me *or a 6-month waitlist. Participants complete pre-study, post-study and monthly surveys about their health and utilisation of health services. A post-study clinical audit will be conducted to validate self-reports about influenza vaccination and visits to the university health service due to influenza-like illness (ILI) amongst a subset of participants. 600 participants older than 18 years with monthly access to the Internet and email will be recruited. Participants who (i) discontinue the online registration process; (ii) report obtaining an influenza vaccination in 2010 before the commencement of the study; or (iii) report being influenced by other participants to undertake influenza vaccination will be excluded from analysis. The primary outcome measure is the number of participants obtaining influenza vaccination during the study. Secondary outcome measures include: number of participants (i) experiencing ILI symptoms, (ii) absent from or experiencing impairment in work or study due to ILI symptoms, (iii) using health services or medications due to ILI symptoms; (iv) expressing positive or negative attitudes or experiences towards influenza vaccination, via their reasons of receiving (or not receiving) influenza vaccine; and (v) their patterns of usage of *Healthy.me *(e.g., frequency and timing of hits, duration of access, uptake of specific functions).

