### Outcome measures

Table 2 outlines the primary and secondary outcome measures in this study. Participants in control and intervention groups who are analysed for primary outcome will have completed the post-study survey and/or provided influenza vaccination status by de-identified clinical audit. Participants in intervention group who had the opportunity to use *Healthy.me *but did not do so will be included in the primary analysis. Participants who met the exclusion criteria or whose influenza vaccination status was unavailable at study completion will be excluded.

**Table 2 T2:** Primary and secondary outcome measures collected at different time points

Outcome measure	Measurement timepoints & methods
*Primary outcome*	
Proportion of participants obtaining influenza vaccination during the study	• Study completion^1 ^(via self-reports and clinical audit)
*Secondary outcome*	
Proportion of participants visiting the University Health Service during the study	• Study completion^1 ^(via self-reports and clinical audit)
*Ancillary outcomes*	
Proportion of participants experiencing symptoms of influenza-like illness ^2 ^(ILI) during the study	• Monthly from study commencement in May to October 2010 (via self-reports)
Proportion of participants using medications or remedy due to ILI symptoms ^2^	• Monthly from study commencement in May to October 2010 (via self-reports)
Proportion of participants visiting a healthcare professional due to ILI symptoms ^2^	• Monthly from study commencement in May to October 2010 (via self-reports)
Proportion of participants experiencing impairment in work or study due to ILI symptoms ^2^	• Monthly from study commencement in May to October 2010 (via self-reports)
Number of days absent from work or study due to ILI symptoms (per participant)	• Monthly from study commencement in May to October 2010 (via self-reports)
Reasons for receiving (or not receiving) influenza vaccine	• Study completion^1 ^(via self-reports)
Patterns of usage and feedback of PCHMS	• Study completion^1 ^(via automatic system logs, data entered by participants into PCHMS, and self-reports)

^1^Estimated end of average respiratory disease and influenza season in Southern Hemisphere (i.e. October 2010, six months from study commencement)

^2^Defined by case definitions of influenza (fever with cough or a sore throat) issued by NSW Health and Centers for Disease Control and Prevention (CDC) as of 26 March 2010

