### Data collection

Four methods will be used to collect data about participants during the study:

*Surveys*: Questions are informed by studies tracking ILI symptoms in the Australian community [19,20], and studies investigating influenza experiences and attitudes amongst university students and healthy working adults [14,21-26]. The following surveys will be conducted:

• Pre-study survey to obtain participant demographics and health status at study registration.

• Monthly one-minute follow-up surveys to obtain participant self-reported symptoms of ILI, use of health services, and impact on work and study due to ILI symptoms throughout the study.

• Post-study survey to obtain participant influenza vaccination status. For those who receive *Healthy.me *intervention, they will be asked in addition for their perceived usefulness of *Healthy.me*.

*System logs*: During the study, participant actions on *Healthy.me *will be unobtrusively logged.

*Personal health data*: Data entered by participants into *Healthy.me *about their health (e.g., medications used, scheduled tasks and appointments, members in healthcare team).

*Clinical audit*: This will be conducted post-study for patients at the University Health Service (UHS), to validate self-reports of vaccination and visits to a healthcare professional related to ILI symptoms for a subset of participants before and during the study. Clinical audits will be conducted on site at the UHS, linking UHS patient records with our survey data using exact matches on participants' surname, date of birth, and an approximate match on first-name. Extracted records will be replaced with a de-identified ID, and all names will be removed prior to analysis.

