#### Baseline comparisons

Comparisons of baseline variables between PCHMS and waitlist groups will be conducted using Student's t-tests for continuous variables and χ^2 ^tests for categorical variables, to assess whether randomisation was performed properly. Adjustment for baseline characteristics is planned to correct for possible imbalance between the randomised groups and to provide a stratified estimate of the effect of intervention if applied [29,30].

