#### Secondary and ancillary analyses

Differences in proportions of participants between different groups (e.g. waiting list vs. PCHMS; used PCHMS once vs. used PCHMS more than once) will be examined using χ^2 ^test for each of the following activities experienced at least once during the study: i) visited the University Health Service (or a healthcare professional); ii) used medications or remedy; and iii) experienced performance impairment. Differences in average number of days of absence per participant will be compared between waitlist and PCHMS groups using Student's t-test. Reasons for receiving (or not receiving) influenza vaccine and impact of ILI symptoms will be reported using descriptive statistics.

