• *Social influence and access to Healthy.me*: The social networks of individual participants may span the intervention and control arms of this study, and see intervention subjects un-blind control subjects with information obtained from the intervention. As this is a pragmatic trial in the real world, such effects cannot be controlled for. Indeed participants' social networks are likely to influence access to Healthy.me if the intervention was in routine use. We will attempt to measure this effect by asking participants in the control arm if they have been in contact with intervention arm subjects. If a significant group is identified, we will conduct separate analyses to estimate the impact of any such effect on overall trial results.

• *Baseline comparisons*: As this is a pragmatic trial of a multifaceted intervention in a complex environment, it is possible that baseline variables associated with subjects might also influence the outcome. For example, having a prior history of obtaining influenza vaccination may predict future vaccination rates, independently of any additional intervention. We will identify potential baseline variables that might influence outcome, including gender, and test for unequal distribution of these variables in the intervention and control populations. Should there be a significant difference in their distribution due to chance bias, these will be fitted in an analysis of covariance to model their impact on any observed differences between the two arms [39].

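### The University Health Service visit outcome is compared by an unadjusted chi-square test although a 12-month baseline audit of the same service's records is already scheduled, so some precision may be lost

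*Protocol article*

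**What the plan says.** **Baseline data.** Protocol article, Study procedure, Table 3, schedules under Baseline: "Data from de-identified clinical audit from previous 12 months: electronic extraction (collected post-study"). The Data collection section says what the audit is for: checking self-reported vaccination and ILI-related visits against UHS records, "for a subset of participants before and during the study".

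**Outcome.** Outcome measures, Table 2, has one row under its secondary heading: "Proportion of participants visiting the University Health Service during the study". It is measured at study completion by self-report and audit, and it is the outcome closest to the second hypothesis, on use of services.

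**Analysis.** Under Secondary and ancillary analyses, differences in proportions "will be examined using χ^2 ^test for each of the following activities experienced at least once during the study". The first activity listed is "visited the University Health Service (or a healthcare professional"). No covariate is named. The only adjusted model set out in detail, the sequential logistic regression under Primary analysis, is for vaccination and does not name prior UHS use.

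**General adjustment.** Baseline comparisons states: "Adjustment for baseline characteristics is planned to correct for possible imbalance between the randomised groups". Limitations, on baseline variables that might influence outcome, states: "Should there be a significant difference in their distribution due to chance bias, these will be fitted in an analysis of covariance".

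**The concern.** Someone who attended the UHS in the past year is plausibly more likely to attend during the study than someone who never uses it. The earlier records come from the same service as the outcome. If dated before registration, they cannot be affected by allocation, even though they are extracted after the study. A covariate of this kind is what an adjusted comparison of UHS visits would want, yet the stated comparison leaves it out.

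At stake is the width of the confidence interval, and hence the power, for the service-use hypothesis. A chance difference between arms in the share of regular UHS users would also stay in the estimate unless it happened to trigger the conditional adjustment.

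**Working it through.** **1. The plan's own figure.** The only stated sample size is for vaccination: 15% vs 25%, two-sided 5%, 80% power, about 10% dropout, 600 in total.

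- Without continuity correction: [1.96·√(2·0.20·0.80) + 0.842·√(0.15·0.85 + 0.25·0.75)]² / 0.10² ≈ 250 per arm.
- With continuity correction: (250/4)·[1 + √(1 + 4/(250·0.10))]² = 62.5 × 2.077² ≈ 270 per arm.
- Allowing for dropout: 270/0.90 = 300 per arm, 600 in total.

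The stated figure reproduces. No size or power is stated for UHS visits, so no stated figure is wrong. I use 270 analysed per arm below.

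**2. Variance explained by prior attendance.** The documents do not give these inputs, so they are assumptions. Let 40% have attended in the prior year.

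- *Stronger link*: 50% of prior attenders and 15% of the others attend during the study. Overall rate 0.4·0.50 + 0.6·0.15 = 0.29. Between-group variance 0.4·0.6·0.35² = 0.0294. Total variance 0.29·0.71 = 0.2059. R² = 0.0294/0.2059 = 0.143. Standard-error ratio √(1 − 0.143) = 0.926. Equivalent sample 1/(1 − 0.143) = 1.167, about 17% more participants.
- *Weaker link*: 40% vs 20%. Overall rate 0.28. Between-group variance 0.4·0.6·0.20² = 0.0096. Total variance 0.28·0.72 = 0.2016. R² = 0.048. Standard-error ratio 0.976. Equivalent sample 1.05, about 5% more.

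The corresponding correlations are √0.143 ≈ 0.38 and √0.048 ≈ 0.22.

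**3. Power.** With correlation r between prior and in-study attendance, the effective sample is about 270/(1 − r²) per arm. The UHS rates are again assumed.

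| r | 1 − r² | effective n per arm | power, 30% vs 40% | power, 15% vs 25% |
|---|---|---|---|---|
| unadjusted | 1.00 | 270 | 68.4% | 83.0% |
| 0.1 | 0.99 | 273 | 68.8% | 83.3% |
| 0.2 | 0.96 | 281 | 70.2% | 84.4% |
| 0.3 | 0.91 | 297 | 72.5% | 86.3% |
| 0.4 | 0.84 | 321 | 75.9% | 88.9% |
| 0.5 | 0.75 | 360 | 80.4% | 92.0% |

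A simulation (6,000 trials per setting, 40% prior attenders, 30% vs 40%) compared the chi-square test with a Mantel-Haenszel test stratified on prior visit. It gave 68.7% and 72.6% at r = 0.3, and 68.5% and 75.0% at r = 0.4, in line with the table.

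**4. Chance imbalance under the stronger link.** The standard error of the difference in prior attendance is √(2·0.4·0.6/270) = 0.042, so the 95% range is about ±8 points. Multiplied by the 35-point gap, this moves the unadjusted risk difference by up to about ±3 points. That variation is already part of the chi-square test's error. Adjustment removes it.

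**5. Do the general statements secure this gain?** No. Baseline comparisons names neither the outcome nor the covariate. Limitations adjusts only after a significant imbalance, so whenever the arms look balanced the covariate stays out and its precision gain is forgone.

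**The case against.** The strongest reply is that nothing here is an error. In a 1:1 randomised trial the unadjusted chi-square test is valid, and covariate detail for a secondary outcome can be left to a full analysis plan that is not shown. The validity point stands in full. The second stands only in part, because the article does not leave the method open: it names the test for this outcome.

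Four stronger readings are tempting and should not be adopted.

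- *The baseline audit is collected and then wasted.* Data collection gives it a validation purpose. It is unused only in the between-arm comparison.
- *Chance imbalance is left uncorrected.* Baseline comparisons and Limitations both provide for adjustment, and the audit sits in the Baseline stage. That provision is general or conditional, but it exists.
- *The look-back counts post-randomisation visits as baseline.* Table 3 gives no anchor date, and access periods vary with registration date. The harm, however, needs a common reference date later than some registrations, and the text states none. Taken as 12 months before study start, it does not arise.
- *UHS visits are the trial's only secondary outcome.* That is true of Table 2, but the abstract lists others: "Secondary outcome measures include: number of participants (i) experiencing ILI symptoms" opens its list.

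A further objection has weight: the audit is described as covering a subset and, for visits, those related to ILI. Table 3 does not say that the baseline extraction covers all UHS visits. If it does not, prior prevalence and predictive strength could be well below what is assumed here. Linkage on surname, date of birth and approximate first name will also misclassify some people. Because the records predate allocation, this weakens the covariate without biasing the comparison.

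**Conclusion.** The point holds as lost efficiency, not as error or bias. A baseline measure from the same source as the UHS-visit outcome is scheduled, the stated comparison does not use it, and the adjustment clauses do not secure its use. Illustratively, the loss equals 5% to 17% more participants (R² 0.048 to 0.143). In power terms it is under 2 points for r up to 0.2, about 3 to 8 points for r of 0.3 to 0.4, and about 9 to 12 points at r = 0.5. All of this rests on assumed attendance rates and correlations and on 270 analysed per arm. The documents supply no UHS attendance rate or correlation, so the true gain could be small.

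**What to change.** Prespecify, independently of any baseline significance test, a logistic regression of the Table 2 outcome (UHS visit, yes/no) on arm with one covariate: any UHS visit recorded by the audit in the 12 months before the participant's own registration date. Code participants with no matching record as having no prior visit. Obtain the adjusted risk difference by standardising over the covariate and report it with its 95% CI. A Mantel-Haenszel analysis stratified on the same variable would serve equally well. Keep the chi-square test as unadjusted support.

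State in Table 3 that the look-back ends at each participant's registration, and that the baseline extraction covers the same type of UHS visit as the outcome, not only ILI-related visits.

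The cost is analysis wording if the scheduled extraction already has that scope. If it was planned for ILI-related visits or a subset only, the extraction must be widened, within whatever the consent and ethics approval allow.

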#### Intervention group and exposure

The period of access to *Healthy.me *will vary depending on the date of participant registration. During the study *Healthy.me *will provide participants in the intervention group with information and forward email reminders about influenza, indications for vaccination, as well as an email link to the University Health Service for participants to book an appointment for influenza vaccination or other medical concerns, should they wish to use that service (Figure 4).

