#### Randomisation and allocation concealment

After consent each participant is randomly allocated to the intervention or control group, facilitated by a computerised centralised allocation process which forms part of the online registration procedure. Eligible healthcare consumers are randomly assigned to the intervention or control group using a computer generated random number sequence in randomly assigned blocks (block sizes 2, 4 and 8) with intervention allocation ratio of 1:1 [32].

The randomisation sequence generation, participant registration, and group allocation processes are computerised online and do not involve human interventions from the investigators. The block randomisation sequence is pre-generated by a member external to the research team using a computerised random-number generator before commencing participant recruitment. As each participant completes the online registration procedure, he/she receives the next consecutive allocation in the sequence, which automatically assigns the consumer to the intervention or control group.

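### The first monthly survey's recall window reaches back before randomisation, so illness preceding allocation enters ancillary outcomes meant to count events in the study

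*Protocol article*

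**What the plan says.** Four statements in the protocol article bear on this.

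- **Allocation is individual and rolling.** Randomisation and allocation concealment: "As each participant completes the online registration procedure, he/she receives the next consecutive allocation in the sequence". Intervention group and exposure adds that the period of access "will vary depending on the date of participant registration".
- **Surveys follow the calendar.** Study procedure: "From the time participants are recruited until study completion", every participant "will receive an email in the first week of each month to complete a one-minute survey about their health in the past month". No rule shortens the first window or ties it to the registration date.
- **Five ancillary outcomes rest on these surveys.** Table 2 lists influenza-like illness (ILI) symptoms, medication use, visits to a healthcare professional, impairment and days absent, each timed "Monthly from study commencement in May to October 2010 (via self-reports". The first four are proportions and the last is a count per participant.
- **Scoring.** Secondary and ancillary analyses compares proportions by chi-square for "each of the following activities experienced at least once during the study", listing health-service visits, medication use and impairment. Mean days absent is compared by t-test.

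On the calendar, Study procedure states: "The duration of the study is expected to be six months from May 2010 to October 2010". The Table 2 footnote defines study completion as "Estimated end of average respiratory disease and influenza season in Southern Hemisphere (i.e. October 2010, six months from study commencement".

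**The concern.** Someone who registers late in a month receives the first survey within days and is asked about a month that lies almost wholly before allocation. An episode in that period cannot have been influenced by the intervention. Under the at-least-once rule, one such episode makes the participant a case for the whole study, whatever happens afterwards. The outcome definition (events in the study) and the data collection rule (a fixed one-month look-back) therefore disagree for every participant's first survey.

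At stake are the size and precision of the between-arm comparisons on some ancillary outcomes, and the meaning of the reported proportions, which are raised in both arms.

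A smaller question arises at the other end. If the last monthly mailing is in early October, it looks back on September, and the protocol does not say where ILI in October would be recorded.

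**Working it through.** The plan gives no figure on this point. Its sample size of 600 concerns the primary outcome and is not in question here.

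**1. Share of the first window before randomisation.** Assumptions: a 30-day look-back, and registration equally likely on each of the 30 days before the first survey. A participant who registers *j* days before the survey has (30 − *j*)/30 of the window before allocation. This runs from 0 (*j* = 30) to 29/30 = 97% (*j* = 1). The mean is 14.5/30 = 48%, or about one half.

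**2. Share of all recalled time.** Divide one half by the mean number of surveys per participant. The protocol does not give the spread of recruitment. Assuming an even spread over the first 1 to 4 months:

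| Last survey at | Recruitment over 1 month | Recruitment over 4 months |
|---|---|---|
| month 6 | 0.5/6 = 8.3% | 0.5/4.5 = 11.1% |
| month 5 | 0.5/5 = 10.0% | 0.5/3.5 = 14.3% |

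This is a share of time. It is not the bias on the planned scales, which steps 3 and 4 give.

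**3. At-least-once proportions.** Let *q* be the risk of an event in the pre-randomisation part of the window. It is equal in both arms by randomisation and is taken as independent of later events. Let *p* be the true post-randomisation risk.

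- Observed risk = 1 − (1 − *q*)(1 − *p*) = *q* + (1 − *q*)*p*.
- Observed risk difference = (1 − *q*) × true risk difference.

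The relative shrinkage is therefore *q*. For half a month at monthly risk *r*, *q* = 1 − √(1 − *r*):

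| Assumed monthly risk *r* | *q* |
|---|---|
| 5% | 1 − √0.95 = 2.5% |
| 10% | 1 − √0.90 = 5.1% |
| 20% | 1 − √0.80 = 10.6% |

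The shrinkage of the risk difference does not depend on the number of surveys. The risk ratio does. An illustration at 10% monthly risk, with an assumed true hazard ratio of 0.70 (neither figure is from the protocol) and the 48% from step 1:

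| Surveys | Risk difference, true → observed | Risk ratio, true → observed |
|---|---|---|
| 1 | 0.0156 → 0.0148 | 0.71 → 0.85 |
| 3 | 0.0635 → 0.0604 | 0.73 → 0.78 |
| 5 | 0.0953 → 0.0906 | 0.75 → 0.78 |

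**4. Mean days absent.** Observed days are post-randomisation days plus pre-randomisation days. The second term has the same expectation in both arms and cancels from the difference in means. If the two terms are independent or positively correlated, the variance rises, so the t-test loses some power without bias.

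**5. ILI occurrence.** The analysis section lists no between-arm test for having ILI symptoms. The reported proportions would be raised in both arms, to *q* + (1 − *q*)*p*.

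**6. October.** A last mailing on 1 to 7 October has a window ending 30 September to 6 October. That would leave 31 to 25 October days of the 184 from 1 May to 31 October (17% to 14%) without a monthly survey. A mailing in the first week of November would cover them. Table 2's May-to-October timing can be read in two ways:

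- as mailing months, in which case a survey in early May looks back mainly on April;
- as months covered, in which case the last mailing falls in November, after the stated completion.

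The text does not settle which is meant.

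**The case against.** **The questionnaire is not shown.** One line in a journal article may paraphrase a form that already asks about time since joining, or the analysis may drop earlier events. That is possible, and it would close the gap. But the article does more than stay silent: it states both the send date and the look-back, and together they do not fit outcomes confined to the study. If the form differs, the description needs correcting.

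**Randomisation balances the extra events.** This stands. A reader might infer that one arm is favoured, but nothing in the protocol supports that, because pre-allocation illness has the same expected frequency in both arms.

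**The dilution is easily overstated.** A reader might take the 8% to 14% share of recalled time as the shrinkage of every arm difference in all five outcomes. The planned analyses do not bear this out. The at-least-once proportions shrink by *q*, mean days absent does not shrink, and no between-arm test of ILI occurrence is listed.

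**Loss of October data is not demonstrated.** A reader might conclude from the Data collection section, which describes the post-study survey as obtaining vaccination status, that ILI in October goes unrecorded. That description is not exhaustive. The Primary analysis section has contact with children and past vaccination collected at post-study, and Table 2 places reasons for vaccination and self-reported University Health Service visits at study completion. The date of the last monthly mailing is not given either. This is an ambiguity to clear up and no more.

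**Only ancillary outcomes are touched.** This also stands, and it limits the importance of the point.

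**Conclusion.** The point holds in a limited form. Followed as written, the survey rule counts pre-randomisation illness in ancillary outcomes meant to cover the study period. About half of each participant's first window is affected if registration is even within the month.

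For visits to a healthcare professional, medication use and impairment, the risk difference shrinks by about 2.5% to 11% at assumed monthly risks of 5% to 20%. This takes pre- and post-randomisation events as independent and earlier events as reported alike in both arms. Mean days absent keeps its expected difference but loses precision. The primary outcome and the University Health Service visit outcome are measured at study completion and are not affected by this window.

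The event risks and the registration pattern are assumptions, since the protocol gives neither. This is a minor point, worth acting on because it is cheap to prevent and because undated past-month answers cannot reliably be split afterwards.

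**What to change.** Word each participant's first monthly survey 'since you registered on [date]', with the date filled in by the online system, and state that only events after registration count towards the ancillary outcomes. Later surveys can keep the one-month look-back. The cost is one wording change and slightly fewer counted events.

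Separately, state the date of the last monthly mailing and whether an early-November survey or the post-study survey records ILI in October, so that collection matches the May-to-October timing in Table 2. This costs one sentence if October is already covered. If it is not, it costs one further mailing or the same short ILI items added to the post-study survey.
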